### Study design

2.1

This prospective, single-center, randomized, single-blind, placebo-controlled study will enroll 250 healthy participants. Participants will undergo acupuncture in separate sessions at one of seven predefined acupoints (verum acupuncture) and its corresponding non-acupoint (sham acupuncture), with a 1-week interval between sessions (18) (Figure 1). All participants will undergo two identical fMRI scanning sessions, separated by a 1-week interval, which corresponds to the washout period between the two acupuncture interventions. Each session will include resting-state fMRI scans before and after acupuncture, as well as task-based fMRI scans during acupuncture (Figure 2). The sequence of verum and sham protocols will be randomized across all fMRI runs, and the order of presentation will be counterbalanced across subjects (18).

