### Sample size

2.3

Currently, there are no standardized criteria for determining sample sizes in MRI studies, as they are often constrained by practical considerations such as scanning time and cost. Based on an efficiency analysis of sample size estimation in MRI research, a previous study indicated that approximately 12 participants are required to achieve 80% power at the single-voxel level for typical activation effects (19). In line with this reference and considering the study design, we set a sample size of 30 participants per acupuncture point. Each volunteer will undergo both verum and sham acupuncture at the same acupoint, resulting in a total of 210 experimental sessions. To account for potential data loss due to head motion or participant dropout, we plan to enroll a total of 250 subjects.

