#### MRI scanning protocol

2.6.2

The fMRI data will be acquired with the Siemens Prisma 3.0T MRI (Siemens, Munich, Germany) at the Shenzhen Traditional Chinese Medicine Hospital, Shenzhen, China. High-resolution T1-weighted structural images will be acquired using a magnetization-prepared rapid gradient-echo (MPRAGE) sequence with the following parameters: repetition time (TR) = 2,200 ms, echo time (TE) = 2.45 ms, field of view (FOV) = 256 mm × 256 mm, isotropic voxel resolution = 1 × 1 × 1 mm^3^, 175 slices with no interslice gap, and a flip angle (FA) of 8°. For resting-state and task-based functional scans, the parameters will be as follows: TR = 2,000 ms, TE = 30 ms, 37 slices, in-plane resolution = 64 × 64, voxel resolution = 3.75 × 3.75 × 4 mm^3^, and 240 volumes acquired per run. Before the scanning session, participants will be positioned supine with their heads immobilized using a pillow. They will be instructed to keep their eyes closed, remain relaxed, avoid deliberate mental activity, and breathe naturally. Foam earplugs are provided to minimize scanner noise. Scanning commences after participants have acclimated to the environment.

Both verum and sham acupuncture protocols will follow the procedure below (Figure 2). After 20 min of quiet rest, the subject will first undergo a 14-s locator scan to determine the imaging range. This will be followed by a 4-min and 39-s 3D high-resolution T1-weighted imaging sequence to acquire anatomical structural information. A pre-acupuncture resting-state fMRI scan lasting 6 min and 6 s will then be performed. Subsequently, a licensed acupuncturist will enter the MRI scanning room to administer acupuncture on the right limb using a block paradigm: three 60-s cycles of twisting needle manipulation will alternate with three 60-s cycles of needle-retaining baseline states. Concurrently, task-based fMRI scanning will be conducted for 6 min and 6 s. Following needle removal, a 6-min and 6-s post-acupuncture resting-state fMRI scan will be acquired.

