#### Statistical analysis

2.7.3

Neuroimaging analyses will be conducted using the SPM12 toolbox on the MATLAB platform. First, one-sample *t*-tests will be performed to identify brain activation patterns associated with verum acupuncture (at true acupoints) and sham acupuncture (at non-acupoints). Subsequently, repeated-measures analysis of variance (ANOVA) will be applied. If statistically significant effects are detected, paired-sample t-tests will be conducted between the two groups to identify differential brain activation patterns between true acupoints and non-acupoints. Additionally, paired-sample *t*-tests will be performed to compare: (1) Resting-state functional activity pre- versus post-acupuncture; (2) Resting-state activity (pre-acupuncture) versus task-based activity (during acupuncture). A voxel-wise threshold of *p* < 0.005 with a false discovery rate-corrected cluster level of *p* < 0.05 was applied in the task fMRI analysis. Significant activation clusters will be visualized and localized using the xjView, MRIcron, and BrainNet Viewer toolboxes within the MATLAB platform.

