#### Pre- vs. post-acupuncture changes

3.2.1

Following verum acupuncture, significant reorganization of resting-state functional connectivity occurs compared to sham acupuncture. This includes weakened connectivity within the default mode network (DMN), suggesting that the brain may remain less prone to mind-wandering even at rest; enhanced coupling between the salience network (SN) and the central executive network (CEN), indicating a potential improvement in the brain’s ability to flexibly switch between internal Deqi sensation and external tasks; and reduced hyper-connectivity among pain-related regions such as S1, S2, thalamus, and anterior insula, which may underlie its long-term analgesic effects.

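### The task verum–sham contrast leaves out the randomised session order; grouping by order is a cheap refinement that helps only if the response to stimulation changes between sessions

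*Protocol article*

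**What the plan says.** Section 2.1 (Study design) describes a two-session crossover: "The sequence of verum and sham protocols will be randomized across all fMRI runs, and the order of presentation will be counterbalanced across subjects". The sessions are "separated by a 1-week interval, which corresponds to the washout period between the two acupuncture interventions".

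Section 2.3 (Sample size) sizes the study by acupoint: "we set a sample size of 30 participants per acupuncture point". It expects losses: "To account for potential data loss due to head motion or participant dropout, we plan to enroll a total of 250 subjects".

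In section 2.6.2 the task signal is a contrast within one run: "three 60-s cycles of twisting needle manipulation will alternate with three 60-s cycles of needle-retaining baseline states".

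Section 2.7.3 (Statistical analysis) starts the verum–sham comparison with a repeated-measures ANOVA whose factors are not named. If that is significant, "paired-sample t-tests will be conducted between the two groups to identify differential brain activation patterns between true acupoints and non-acupoints". Section 2.7 names no order, period or sequence term. The resting-state tests listed in 2.7.3 compare before with after acupuncture, and rest with task. No verum–sham test of resting change is listed, although section 3.2.1 anticipates such a result: "significant reorganization of resting-state functional connectivity occurs compared to sham acupuncture".

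**The concern.** Order is controlled in the design and then dropped from the test that identifies verum–sham differences. A shift that affects a whole session equally is not the problem, because it largely cancels in the contrast of manipulation with retained-needle blocks inside the run. What can remain is a response to stimulation that is larger in one session than in the other, for example because needling is new the first time.

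Such an effect raises the verum-minus-sham difference in participants who had verum first and lowers it in those who had sham first. A paired t-test counts that spread as random error. If exclusions leave the two orders unequal within an acupoint, part of it also enters the estimate. At stake is some sensitivity in the contrast meant to separate specific from non-specific effects. The validity of the contrast is not at stake.

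**Working it through.** **Inputs from the article.** There are 30 participants per acupoint and seven acupoints, so 7 × 30 = 210. With 250 enrolled the allowance is 40/250 = 16%. The voxel threshold is p < 0.005, sidedness not stated, with a cluster-level correction. The article gives no power figure for the verum–sham contrast. Its reference value of about 12 participants for 80% power comes without effect size or alpha, so there is no stated figure to reproduce.

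**Assumptions.** The verum–sham effect is d = 0.5. SD is 1 for the paired difference within an order. The contrast is tested separately in each acupoint. The session-by-stimulation effect δ is 0, 0.1, 0.25 or 0.5 SD.

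**Model.** The paired difference has mean τ + δ if verum came first and τ − δ if sham came first. With n1 and n2 participants in the two orders and n = 30:

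- Bias of the paired mean = δ(n1 − n2)/n.
- Expected variance used by the paired test = 1 + 4δ²n1n2/[n(n − 1)].
- Adjusted estimate = half the sum of the two order means, with standard error 0.5√(1/n1 + 1/n2) and 28 df instead of 29.

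**Balanced order, 15:15.** The bias is 0. For δ = 0.5 the variance used is 1 + 7.5/29 = 1.26 where 1 would be right. For 0.25 it is 1 + 1.875/29 = 1.06, and for 0.1 it is 1 + 0.3/29 = 1.01. Power at d = 0.5 and type I error, both two-sided 0.05:

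| δ | Paired power | Adjusted power | Paired type I error |
|---|---|---|---|
| 0 | 0.754 | 0.753 | 0.050 |
| 0.1 | 0.751 | 0.753 | 0.049 |
| 0.25 | 0.733 | 0.753 | 0.044 |
| 0.5 | 0.672 | 0.753 | 0.029 |

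At the voxel threshold of 0.005, taken as one-sided, paired power for δ = 0, 0.25 and 0.5 is 0.50, 0.47 and 0.38, against 0.50 adjusted.

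**Order 17:13.** For δ = 0.25 and 0.5 the bias is 0.25 × 4/30 = 0.033 and 0.5 × 4/30 = 0.067 SD. Paired power is 0.673 and 0.539 if sham-first is in excess under habituation, and 0.788 and 0.788 if verum-first is. The averages are (0.673 + 0.788)/2 = 0.73 and (0.539 + 0.788)/2 = 0.66, within about one point of the 15:15 values. Adjusted power is 0.745. Two-sided type I error is 0.047 and 0.039.

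**Order 18:12.** Two-sided type I error is 0.051 and 0.053. At one-sided 0.005, the error in the direction of the bias is about 0.009 and 0.010.

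**How likely is imbalance?** Assume that order starts balanced within each acupoint (35 or 36 enrolled) and that random losses bring it to 30. The hypergeometric probability is then 0.177 per acupoint for 17:13 or worse, and 0.019 for 18:12 or worse. The article states balance only across subjects, so the starting point is an assumption.

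**Whole-session shift.** A simulated additive shift of 0.5 SD for the whole session leaves the paired test at power 0.75 and type I error 0.050, at 15:15 and at 17:13 alike.

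**The case against.** The paired t-test is a standard analysis for a crossover with randomised, counterbalanced order, and counterbalancing is itself a way to handle order. The ANOVA that comes first has unnamed factors, so order may be among them, and a full analysis plan may say more. That stands, and it is why the point concerns only the follow-up test that the article does name.

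The benefit also rests on an effect that the article does not report. At 0.1 SD it is nil. At 0.5 SD the session effect is as large as the assumed verum–sham effect, which is a demanding assumption. The power figures are for a single voxel and do not translate directly into detection under the planned cluster-level inference. These points stand too.

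A reader might infer that losses could cut power to 0.54. That is one of two equally likely directions under random loss; the other gives 0.79. A reader might also infer that the chance of 17:13 or worse in at least one of seven acupoints, 1 − (1 − 0.177)⁷ = 75%, means a likely failure. It describes a small bias in one or a few acupoints, with two-sided type I error still below 0.05.

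**Conclusion.** The point holds as a cheap improvement. The named task contrast discards the randomised order. If the response to stimulation differs between sessions by 0.25 to 0.5 SD, this costs about 2 to 8 points of single-voxel power at balanced order (0.753 − 0.733 and 0.753 − 0.672). It costs essentially nothing at 0.1 SD or below. Imbalance from losses adds a bias of 0.03 to 0.07 SD at 17:13, in either direction, with little change in average power and no material inflation of two-sided type I error.

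A reader might conclude that the paired test is invalid, or that a general drift between visits contaminates it. The documents support neither. With balanced order the test is unbiased and errs on the conservative side, and a whole-session shift cancels within the run. Nor is a resting-state verum–sham paired test at fault, since section 2.7.3 names none. The size of the gain depends throughout on the assumed session effect, d = 0.5 and separate analysis of 30 participants per acupoint.

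**What to change.** In section 2.7.3, replace the paired verum–sham t-test for the task data. Form each participant's verum-minus-sham contrast image and enter the images in a two-sample SPM12 design grouped by order (verum first, sham first), with equal variances. Test the verum–sham effect with contrast [0.5 0.5]. If a verum–sham comparison of resting change is made, use the same order-grouped design for the difference in pre-to-post change. That would be an addition, not a replacement.

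The change needs wording and a different group-level design on data already collected. It costs one degree of freedom per acupoint (29 to 28). With no session effect, power goes from 0.754 to 0.753 at 15:15, to 0.745 at 17:13 and to 0.736 at 18:12. Grouping by order does not remove carryover from the first session into the second, which still depends on the one-week washout.

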**Methods:**

We designed a randomized, single-blind, controlled trial. To achieve high statistical power and generalizability, 250 healthy participants will be enrolled. Each participant will undergo acupuncture at one of seven predefined acupoints (verum) and its corresponding non-acupoint (sham control) in two separate sessions, with a 1-week interval. Each session includes: (1) resting-state fMRI before and after needle manipulation, and (2) task-fMRI during the manipulation. The primary outcomes are fMRI-derived brain activity and functional connectivity patterns. Blinding assessment and the Modified Massachusetts General Hospital Acupuncture Sensation Scale-Chinese version (C-MMASS) will be collected to evaluate the credibility of sham control and the Deqi sensation.

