#### Functional connectivity and network analysis

2.7.2

Resting-state functional connectivity (FC) analysis was employed to investigate the synchronized activity between brain regions (23, 24). Specifically, we utilized seed-based correlation analysis, a widely used method to quantify FC between specific regions of interest (25). Following standard resting-state fMRI preprocessing, the mean time series will be extracted from a predefined seed region of interest (ROI). Whole-brain connectivity maps will be generated by computing Pearson’s correlation coefficients between the seed time series and the time series of every other voxel in the brain. The resulting correlation coefficients (*r*-values) will be converted to *Z*-scores using Fisher’s *Z*-transformation to normalize their distribution for subsequent group-level statistical analysis.

The resulting connectivity matrices were then used to construct brain networks where nodes were defined according to the Dosenbach-160 atlas (26), and edges represented the significant FC between node pairs. Subsequently, graph-theoretical analysis was performed to characterize the topological properties of these networks using measures such as clustering coefficient and characteristic path length (27, 28). All analyses were carried out using the GRETNA toolbox (29). Using these nodes and the Fisher’s *Z*-transformed connectivity strengths as weighted edges, we will construct individual functional brain networks for each subject and time point. Key graph-theoretic metrics, including global efficiency (quantifying global integration), local efficiency (quantifying local specialization and fault tolerance), and nodal degree/strength (quantifying regional influence), will be computed from these networks across a range of connection densities to characterize their topological organization robustly.

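### The pre-needling resting scan is used only by subtraction; entering its verum-sham difference as a covariate would make the expected verum-sham resting-state comparison more precise at almost no cost

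*Protocol article*

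**What the plan says.** The Abstract states: "The primary outcomes are fMRI-derived brain activity and functional connectivity patterns". Section 2.1 sets up a within-person comparison: "All participants will undergo two identical fMRI scanning sessions, separated by a 1-week interval", one with verum and one with sham needling, in randomised and counterbalanced order. It adds: "Each session will include resting-state fMRI scans before and after acupuncture, as well as task-based fMRI scans during acupuncture". Section 2.6.2 places the baseline in the sequence of each session: "A pre-acupuncture resting-state fMRI scan lasting 6 min and 6 s will then be performed". Every participant therefore has a same-day baseline for each condition.

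Section 2.7.2 turns the resting scans into seed-based connectivity maps and graph metrics, and says "we will construct individual functional brain networks for each subject and time point".

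Section 2.7.3 then names the tests. After one-sample t-tests, "Subsequently, repeated-measures analysis of variance (ANOVA) will be applied", without naming its factors. A significant ANOVA leads to a verum-sham paired t-test, worded for activation. Two further paired t-tests use the pre-needling scan: "1) Resting-state functional activity pre- versus post-acupuncture", and pre-needling rest against the task run. Neither this section nor any other names a covariate or a baseline adjustment.

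Section 3.2.1 anticipates that after verum needling "significant reorganization of resting-state functional connectivity occurs compared to sham acupuncture".

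**The concern.** Each stated use of the pre-needling scan is a difference. A pre-post paired t-test analyses post minus pre. If the ANOVA includes time, its condition-by-time term is the verum change minus the sham change. Built from these tests with the pre scan in use, the verum-sham contrast of section 3.2.1 is a difference of changes, which fixes the slope on the baseline at 1.

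A slope of 1 suits a baseline that predicts the outcome almost perfectly. Here the comparison is already within person, so each participant's stable level has cancelled. What still links the pre-scan and post-scan differences is the state of that session, blurred by noise from two runs of about six minutes. There is no reason to assume that this link is close to 1. When it is weaker, subtraction carries baseline noise into the contrast.

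At stake is precision on part of the primary outcome, estimated within each acupoint from about 30 people, using scans that will be acquired anyway.

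**Working it through.** **The plan's own figure.** Section 2.3 sets 30 participants per acupoint: 7 × 30 = 210, raised to 250, which corresponds to 210/(1 − 0.16). The step from the cited 12 participants to 30 cannot be reproduced, because no alpha, effect size or SD is given. For scale, a paired t-test at two-sided 0.05 with n = 30 has 80% power at a standardised difference of 0.529.

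**Notation.** For one participant and one connectivity or graph measure:
- D_post = post(verum) − post(sham)
- D_pre = pre(verum) − pre(sham)
- λ = corr(D_pre, D_post), both with variance σ² (assumed equal)

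**Variances of the verum-sham contrast, per participant.**
- Post scan alone: σ²
- Subtraction: Var(D_post − D_pre) = 2(1 − λ)σ²
- Covariate adjustment: (1 − λ²)σ²
- Ratio of adjustment to subtraction: (1 − λ)(1 + λ) / [2(1 − λ)] = (1 + λ)/2

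Subtraction is noisier than ignoring the baseline when 2(1 − λ) > 1, that is, when λ < 0.5.

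**What λ could be.** If r_s is the pre-post correlation within a session and r_b the correlation between scans from different sessions, then λ = (r_s − r_b)/(1 − r_b). Neither is in the document. Examples: r_b = 0.5 with r_s = 0.6 gives 0.1/0.5 = 0.2; r_b = 0.5 with r_s = 0.7 gives 0.4; r_b = 0.7 with r_s = 0.9 gives 0.2/0.3 = 0.67.

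**Power at n = 30.** The effect is fixed so that subtraction has 80% power. Adjustment then works with a standardised effect of 0.529 × √(2/(1 + λ)); at λ = 0.5, for example, 0.529 × 1.155 = 0.611. The last column is simulated with a balanced session-order term in the adjusted model.

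| λ | (1+λ)/2 | Standardised effect, adjusted | Power, subtraction | Power, adjusted |
|---|---|---|---|---|
| 0.2 | 0.60 | 0.683 | 80% | 94–95% |
| 0.5 | 0.75 | 0.611 | 80% | 88% |
| 0.7 | 0.85 | 0.574 | 80% | 85% |
| 0.8 | 0.90 | 0.558 | 80% | 82% |
| 0.9 | 0.95 | 0.543 | 80% | about 80% |

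Estimating the slope costs about 28/27 − 1 ≈ 4% in variance at n = 30, which is why the gain has gone by about λ = 0.9. Type I error was near 5% for both methods.

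**How the covariate must be coded.** The order of sessions is randomised, so D_pre has expectation zero if nothing carries over the week. The effect wanted is the expected D_post at D_pre = 0, which is the intercept when D_pre is entered uncentred. If D_pre is mean-centred (with a balanced order term), the intercept is the plain mean of D_post: the estimate is not adjusted, but its standard error still shrinks. In simulation under no effect, type I error was then about 8–9%, 15% and 23% at λ = 0.5, 0.7 and 0.8.

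**The case against.** The strongest reply is that the plan states no test to which this loss attaches. The quoted pre-post test is within condition and gains nothing from a covariate. The verum-sham paired t-test is worded for activation. The ANOVA's factors are unnamed, and its place in the text suggests task data. Section 3.2.1 describes an expected result and is not an analysis specification. This stands as a limit. A reader might infer that section 2.7.3 prescribes a subtraction test of verum against sham at rest; it does not. What remains is narrower: the expected comparison has to be made somehow, and every listed way of using the pre scan is a difference.

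A second reply is that covariates are commonly left to the analysis plan, which is not shown and may add one. That is possible. The article does, however, name its tests for these scans, so the point concerns a stated choice and does not rest on missing detail.

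Third, change scores are valid. This is accepted. A reader might take the point as a charge of bias or an inflated error rate; neither follows, since subtraction is unbiased with nominal type I error.

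Fourth, λ and the 80% starting power are assumptions, and the power figures are for one univariate test at 0.05. Also accepted. They should not be read as a gain in whole-brain voxel-wise inference, for which no power was calculated. SPM12 group models, moreover, do not readily take a covariate that varies by voxel.

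**Conclusion.** The point holds as one of efficiency. For the verum-versus-sham resting-state comparison at ROI, network or graph-metric level, covariate adjustment estimates the same effect as subtraction, with (1 + λ)/2 of its variance before a cost of about 4% for the slope. From 80% power under subtraction, that is worth about 14–15 points at λ = 0.2, 8 at 0.5, 5 at 0.7, 2 at 0.8 and nothing useful near 0.9. No single gain can be claimed, because the document does not give λ.

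The figures assume equal variances of the pre-scan and post-scan differences, 30 analysable participants per acupoint, randomised order without carry-over into the second baseline, and two-sided 0.05 for one measure. The within-condition pre-post tests are sound and are not part of the criticism.

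**What to change.** Add to section 2.7.3: for ROI or network connectivity and for the graph metrics of section 2.7.2, the verum-sham resting-state effect is estimated per acupoint by regressing the post-scan difference (verum minus sham) on the uncentred pre-scan difference, with session order coded −1/+1. The intercept, which is the effect at zero baseline difference, is reported with its confidence interval. State explicitly that the pre-scan difference is not mean-centred. Keep the within-condition pre-post paired t-tests. Voxel-wise seed maps may keep the change-score contrast.

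The change needs no new scans, participants or staff time at the scanner. It costs one degree of freedom for the slope and one for order, plus a little scripting outside the standard SPM12 group models. It should be fixed before the data are seen.

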### Resting-state fMRI: functional connectivity and network analysis

3.2

This aspect may yield the most intriguing findings, as it reflects the sustained after-effects of acupuncture, rather than immediate responses.

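### The resting-state comparisons listed in section 2.7.3 contain no verum-sham term, so they cannot support the change relative to sham that section 3.2.1 expects

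*Protocol article*

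**What the plan says.** The abstract counts functional connectivity patterns among the primary outcomes. Under Study design (2.1), "Each session will include resting-state fMRI scans before and after acupuncture", and every participant has one verum and one sham session. Pre and post resting scans therefore exist under both conditions.

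Section 2.7.3 sets out the imaging tests in this order:

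- One-sample t-tests of activation under verum and under sham.
- An omnibus step: "repeated-measures analysis of variance (ANOVA) will be applied". No factors, outcome or interaction are named.
- If that is significant, "paired-sample t-tests will be conducted between the two groups to identify differential brain activation patterns between true acupoints and non-acupoints".
- As additional tests, paired t-tests for two comparisons: "Resting-state functional activity pre- versus post-acupuncture", and pre-acupuncture rest against the task run.

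Section 2.7.2 passes the connectivity maps to a later group-level analysis without naming a contrast.

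Section 3.2.1 words the expected result this way: "Following verum acupuncture, significant reorganization of resting-state functional connectivity occurs compared to sham acupuncture". Section 3.2 says of the resting-state part that "it reflects the sustained after-effects of acupuncture, rather than immediate responses".

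**The concern.** A paired pre-post test asks whether connectivity changed during a session. Section 3.2.1 speaks of a change after verum relative to sham, which is a different question. By the scanning procedure in 2.6.2, the post scan always comes after the task run. In both sessions, then, the post scan differs from the pre scan by elapsed time in the scanner, habituation and arousal as well as by needling. The sham session is there to subtract these shared components, and the Introduction makes separating specific from non-specific responses an objective. A pre-post test in the verum session leaves the shared components in. Setting a significant verum test beside a non-significant sham test does not remove them either, because two significance statements are not a test of their difference.

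At stake is the resting-state part of the primary outcome: a verum-specific statement could arise although verum and sham do not differ.

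**Working it through.** **What the plan gives.** Section 2.3 sets 30 participants per acupoint, each with verum and sham, for seven acupoints (7 × 30 = 210; 250 enrolled). It gives no effect size, SD or power for a resting-state contrast, so there is no figure of the plan's own to reproduce. The check uses only n = 30 and the seven acupoints.

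**Assumptions, not in the documents.** One scalar measure. The change scores (post − pre) in the two sessions are bivariate normal with equal SD and equal mean d, in SD units of the change, so there is no true verum-sham difference. The correlation ρ between the two change scores is 0 or 0.5. Tests are two-sided at 0.05.

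**Step 1: verum pre-post test alone.** The statistic is noncentral t with 29 degrees of freedom and noncentrality d√30. P(significant):

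| Drift d | P(significant) |
|---|---|
| 0 | 5.0% |
| 0.2 | 18.5% |
| 0.3 | 35.5% |
| 0.5 | 75.4% |
| 0.6 | 88.8% |

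**Step 2: verum significant in the direction of the drift, sham not.** Simulation, 40,000 trials per setting:

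| Drift d | ρ = 0 | ρ = 0.5 |
|---|---|---|
| 0 | 2.5% | 2.0% |
| 0.1 | 7.0% | 5.5% |
| 0.2 | 14.7% | 11.0% |
| 0.37 | 25.3% | 17.1% |
| 0.6 | 9.8% | 7.6% |
| 0.8 | 1.1% | 1.0% |

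For drifts of 0.2 to 0.6 SD the range is about 8 to 25%. The rate falls again at large drift because both sessions then become significant.

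**Step 3: direct test.** The paired t-test of (post − pre) verum minus (post − pre) sham is significant in a given direction in 2.3 to 2.7% of trials at every drift in the table, that is, at its nominal 2.5%.

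**Step 4: at least one of seven acupoints.** The groups are separate people, so P = 1 − (1 − p)^7.

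- p = 0.0764: 1 − 0.9236^7 ≈ 43%.
- p = 0.251 (a separate run of the d = 0.37, ρ = 0 setting): 1 − 0.749^7 ≈ 87%.
- Comparator, direct test, p = 0.025: 1 − 0.975^7 ≈ 16%.

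**Step 5: a stricter level.** The voxel threshold of 0.005 is stated for task fMRI only. Applied to this single measure as an illustration, the step 2 pattern occurs in about 3 to 4% at d = 0.2 and 17 to 24% at d = 0.6, against 0.25% nominal for the direct test in one direction.

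**Step 6: price of the direct test.** SD of the difference = SD of one change × √(2(1 − ρ)). This gives √1 = 1.0 at ρ = 0.5 and √2 ≈ 1.4 at ρ = 0.

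**The case against.** The strongest reply is that the ANOVA may already contain the missing term. Section 2.7.3 opens with neuroimaging analyses in general and does not restrict the ANOVA to task data. With verum and sham sessions each scanned before and after, condition by time is a natural repeated-measures layout, and a full protocol or analysis plan that is not shown may specify it. This stands in part: the interaction cannot be ruled out, and unnamed factors in a condensed article are not in themselves a fault. But the only follow-up given for the ANOVA concerns activation patterns, and the resting-state tests are listed separately after it, without sham. The mismatch between those tests and section 3.2.1 lies within the article.

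Three stronger readings are tempting, and the documents do not support them:

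- A reader might infer that pre versus post is the only resting-state test. Rest against task is listed too, though it also lacks a sham term.
- A reader might infer that a verum effect will be declared whenever verum is significant and sham is not. No section states such a rule. The plan leaves room for that reading but does not adopt it.
- A reader might take section 3.2.1 as a conclusion. The trial has no data yet and the Results section sets out expectations. Its reference to sham may well mean that a sham comparison is intended but poorly described.

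The drift sizes are also assumptions, and the simulation treats one scalar measure at an uncorrected level. The percentages are not error rates of this plan.

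**Conclusion.** The point holds in a limited form. Neither listed resting-state comparison tests verum against sham, and the expected result in section 3.2.1 needs such a test. Whether the unspecified ANOVA would supply it cannot be told from the article.

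The size depends on a shared drift that the documents do not give. At an assumed 0.2 to 0.6 SD, with n = 30, two-sided 0.05 and no true difference, the verum pre-post test is significant in about 18 to 89%. The pattern of verum significant and sham not occurs in about 8 to 25% per measure and acupoint, against 2.5% for the direct test in that direction. For at least one of seven acupoints it is about 43 to 87%, against about 16%. With no drift, the pattern occurs in about 2% and the problem vanishes. The documents give no reason to assume zero drift, and the direct contrast makes that assumption unnecessary.

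**What to change.** In section 2.7.3, name the condition (verum, sham) by time (pre, post) contrast as the deciding resting-state test. In practice this is the paired test of (post − pre) verum minus (post − pre) sham, applied to the connectivity and graph measures within each acupoint. If the repeated-measures ANOVA is meant to carry this contrast, state its factors. Report the within-session pre-post tests as descriptive, and base any statement relative to sham in section 3.2.1 on the contrast alone.

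The cost is wording only, since all the scans are already planned. The downside is precision: with 1.0 to 1.4 times the SD of a single change score (correlation 0.5 to 0), fewer regions may reach significance.
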